**Table 1 T1:**
[figure not shown]
Population and proportion of sample by census sectors from the city of Santo Anastacio.

**Figure 1 F1:**
[figure not shown]
Distribution and delimitation of the urban census sectors from the city of Santo Anastacio.

### Data collection

2.3

Initially, the evaluators will visit the census sectors drawn and the households that will be part of the sample. In this first evaluation, a face to face interview will be performed using an electronic questionnaire. The questionnaire contains physical activity domains as well as socio-demographic characteristics. After the participants have completed the questionnaires, an accelerometer will be delivered to the research participant with explanations about its use (5-day period). On a pre-scheduled date, the evaluator responsible for delivering the accelerometer will visit to the residence of the participant and perform the accelerometer recall. At that time, the evaluation of cardiac autonomic modulation through analysis of heart rate variability will be scheduled at a predetermined location, being the participant informed about the previous recommendations for this measure procedure – Figure 2.

**Figure 2 F2:**
[figure not shown]
Schematic diagram of research procedures.

### Objective measurement of physical activity

2.4

Subjects will be instructed to wear the accelerometer for 5 days. Messages or phone calls will be sent/made during this period to remind the participant to wear the accelerometer. The objective measurement of physical activity will be performed using the Actigraph GT3X accelerometer (ActiGraph, LLC, Pensacola, FL) which was designed to record movements in 3 orthogonal planes: vertical, horizontal anteroposterior, and medial-lateral.

The accelerometers will be positioned laterally at waist height, and remain in position for 5 full days (3 days of the week and 2 of the weekend).^[9]^ Participants will be instructed on the care of the equipment and required to wear the equipment throughout the day (waking hours), removing the equipment only when there is contact with water (personal hygiene or any kind of aquatic activities) and while sleeping.

The ActiLife 6 program (ActiGraph, LLC, Pensacola, FL) will be used to clean the data. Each data sample, determined from counts, will be summarized considering a specific time interval, this particular interval is designated as an epoch, and lasts for 60 seconds. The 60-second period was selected because it is the closest to the pattern of low intensity and long duration activity.^[10]^ Consecutive hours of zero counts and days with less than 10 hours of monitoring will be excluded.^[11]^

To convert the raw accelerometer data to a more physiological measure, the classification according to activity intensity levels will be used. In this way, the cut-off points recommended by Sasaki et al^[12]^ for adults, performed with the same triaxial accelerometer model, will be employed in the present study. Sedentary activity will be defined as zero counts per minute, light physical activity (<3.00 METs) as less than 2690 counts per minute, moderate physical activity as counts between 2690 and 6166 (3.00–5.99 METs), vigorous physical activity as counts between 6167 and 9642 (6.00–8.99 METs), and very vigorous physical activity as values greater than 9642 counts per minute (≥9 METs).

Thus, the outcomes that will be included in this study, derived from the measurement of physical activity by the accelerometer, will be the counts per minute and total time spent in each intensity of physical activity (light, moderate, vigorous, and very vigorous).

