### Statistics analysis

2.8

After verification of normality by Shapiro-Wilks test, the variables characterizing the sample will be expressed as mean and standard deviation or median and interquartile range. The dependent variable will be the cardiac autonomic modulation. Pearson or Spearman correlation will be used to analyze the relationship between cardiac autonomic modulation and physical activity. Linear regression will evaluate the magnitude of the relationship between cardiac autonomic modulation and physical activity, both in the unadjusted model and in models adjusted by age, schooling, ethnicity, and socioeconomic status. Confounding variables will be inserted simultaneously into the model. It should be emphasized that linear regression analysis will be performed stratifying the study participants by sex. This same type of analysis will be performed to verify the possible relationships between the different domains of physical activity (work, leisure, and displacement activity) and cardiac autonomic modulation.

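### Light-activity time takes in near-still sitting and is tied to wear time, because the sedentary class stops at zero counts, exposure is total minutes, and the models do not adjust for wear

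*Protocol article*

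**What the plan says.** All the processing rules are in section 2.4 of the protocol article (Objective measurement of physical activity).

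- **Lower classes:** "Sedentary activity will be defined as zero counts per minute, light physical activity (<3.00 METs) as less than 2690 counts per minute". The next class starts where light ends: "moderate physical activity as counts between 2690 and 6166 (3.00–5.99 METs". Each minute is classified separately, since of the summary interval the text says "this particular interval is designated as an epoch, and lasts for 60 seconds".
- **Exclusions:** "Consecutive hours of zero counts and days with less than 10 hours of monitoring will be excluded".
- **Schedule:** the device is to "remain in position for 5 full days (3 days of the week and 2 of the weekend", during waking hours.
- **Exposures:** these "will be the counts per minute and total time spent in each intensity of physical activity (light, moderate, vigorous, and very vigorous". Sedentary time is not among them.

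Section 2.8 (Statistics analysis) describes unadjusted regressions and "models adjusted by age, schooling, ethnicity, and socioeconomic status", stratified by sex. Wear time is not in that list.

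**The concern.** Three stated rules act together. First, the sedentary class is a single value, zero, so a seated minute with one recorded count is light activity. Second, exposure is a sum of minutes over valid days, and the 10-hour rule lets participants keep different numbers of days and different hours within them. Third, the models hold neither quantity constant.

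The Introduction hypothesises that activity at higher intensities goes with better autonomic modulation, and section 3 looks to the findings for the best intensity and amount. A light-activity coefficient that partly reflects sitting, and partly how long the device was worn, is hard to place in that picture. If wear time is unrelated to heart rate variability, it adds noise and tends to weaken the light slope. If wear time is related to it, for example through age or health, the slope can move in either direction. The higher classes do not share the problem to the same degree, so it would not cancel when intensities are compared.

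**Working it through.** The article gives no figure for wear time, light minutes or zero-count minutes, so there is no stated figure to reproduce.

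**Step 1. Identity from the stated rules.** For one participant let W be retained wear minutes, Z retained zero-count minutes, M minutes at or above 2690, and L light minutes (counts 1 to 2689). Every retained minute falls in one group, so

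L = W − Z − M.

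If Z is a share s of the time below 2690, then L = (1 − s)(W − M). On the literal reading, with zeros counted as light, L = W − M.

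**Step 2. Illustration.** Assume M = 35 min/day and s = 0.20.

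- 14 h/day: (840 − 35) × 0.80 = 644 min/day. Five valid days give 3220 min and three give 1932 min, a ratio of 3/5 = 0.60, so 40% less with the same daily habits.
- Five days of 10 h: (600 − 35) × 0.80 × 5 = 2260 min. Five days of 16 h: (960 − 35) × 0.80 × 5 = 3700 min. The ratio is 3700/2260 = 1.64.

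Ten hours is the shortest day the plan keeps; 14 and 16 hours are assumptions.

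**Step 3. How strong is the tie?** This needs distributions, all of them assumed. Mean daily wear is normal with mean 840 min and SD 60 or 90, limited to 600–1080. M is gamma with mean 35 and SD 25 min/day, drawn independently of wear. The share s is normal with the means and SDs shown. Valid days are five for all; or three, four, five with probabilities 0.1, 0.2, 0.7; or one to five with 0.03, 0.05, 0.10, 0.20, 0.62. Each scenario has 200,000 simulated persons. Cells give R² of total L with total W; where two values appear, the first is for wear SD 60 and the second for SD 90.

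| Zero share s, mean (SD) | L as share of W | All 5 days | 3–5 days | 1–5 days |
|---|---|---|---|---|
| 0 (0) | 0.96 | 0.85–0.93 | 0.96–0.97 | 0.98–0.99 |
| 0.05 (0.03) | 0.91 | 0.75–0.87 | 0.93–0.94 | 0.97 |
| 0.10 (0.05) | 0.86 | 0.59–0.76 | 0.87–0.89 | 0.94 |
| 0.20 (0.05) | 0.77 | 0.53–0.71 | 0.84–0.87 | 0.92–0.93 |
| 0.20 (0.10) | 0.77 | 0.25–0.43 | 0.61–0.67 | 0.79–0.80 |
| 0.30 (0.10) | 0.67 | 0.21–0.36 | 0.55–0.60 | 0.74–0.76 |
| 0.40 (0.12) | 0.57–0.58 | 0.12–0.23 | 0.39–0.44 | 0.59–0.62 |

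The light shares follow from step 1; for s = 0.20, (840 − 35) × 0.80 / 840 = 0.77.

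**Step 4. Higher intensities.** R² of total M with total W is 0.00 with five days for all, 0.02–0.03 with three to five, and 0.08–0.09 with one to five.

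**Step 5. Is averaging per valid day enough?** R² of L per day with wear per day is 0.12–0.93 whatever the number of days. Averaging removes only the variation in days; hours per day remain.

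**The case against.** The strongest case against the point has four parts.

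- **Zero counts.** Zero is assigned to sedentary before light is defined, so the sensible reading of light is 1 to 2689. That stands: the overlap at zero is a drafting slip, and nothing here relies on it. The absence of any sedentary band above zero remains.
- **Counts per minute.** This exposure is also listed, and it is a rate that does not grow with wear. That stands too, but it does not separate intensities, so it cannot replace the light-time analysis.
- **Condensed article.** A minimum number of valid days, or averaging per day, may be set in a fuller document. This is fair, and it is why the five-day column is shown. It would not change the class boundary or the spread in hours per day. The adjustment set is stated, and it omits wear.
- **Zero-run rule.** Only consecutive hours of zeros are removed, so shorter still periods stay and count as sedentary. That is right, and if such minutes are many and vary between people, the tie to wear loosens, as the lower rows of the table show. The cut-points come from a cited study not at hand, so how often sitting registers a non-zero count is unknown.

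A reader might infer that light time mainly measures how long the device was worn. The documents do not support that: with five valid days for all and a large, variable zero share, R² is as low as 0.12. A reader might also object that the schedule gives weekends 2/5 = 40% of the days against 2/7 = 29% of a week. The same mix is planned for everyone, and no bias in any coefficient follows from what is written.

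**Conclusion.** The point holds as a defect in how one exposure is defined and modelled. By the stated rules, light time absorbs all non-zero time below 2690 and rises with days and hours worn, and the listed covariates do not correct for this. The direction follows from the identity alone. The strength does not: R² with wear is about 0.1 to 0.9 with five valid days for everyone and about 0.4 to 0.97 with three to five, all under assumed wear, zero-share and activity distributions. Minutes at or above 2690 are little affected (0.00 to 0.09), given the assumption that daily minutes at that level are independent of daily wear. The higher-intensity hypothesis is therefore not undermined as a whole; what is weakened is any statement about light activity and its comparison with the other classes. The size of the resulting bias in a regression coefficient cannot be derived from the article.

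**What to change.** 1. Make the classes mutually exclusive: set in advance a non-zero upper bound for sedentary time on the same count scale, with light running from there to 2689. If no bound is adopted, label the class *below 2690 counts (sedentary plus light)* and make no claim about light activity.
2. Replace total time in each intensity by mean minutes per valid day.
3. Add mean daily wear time as a covariate in the regressions of time in each intensity.

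Steps 2 and 3 are both needed, since averaging alone leaves hours per day uncontrolled. Step 1 is needed as well. With the relabelled class including zeros, L = W − M, so at fixed wear its coefficient is exactly minus that of time at or above 2690 and adds no separate finding. Only a real sedentary boundary gives light activity its own information.

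The cost is reprocessing of recorded accelerometer data and one extra covariate in each sex-specific model. No new measurement is required.

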### Domains of physical activity

2.5

Habitual practice of physical activity in different domains will be evaluated by the Baecke et al questionnaire.^[13]^ This instrument evaluates the practice of physical activity in the previous 12 months through 16 questions, considering physical effort at work, the practice of sports activities or systematized exercises in leisure, and leisure activities. In the field of work, questions related to the physical exertion carried out at work include: time spent sitting, standing, and walking in the work environment, carrying weights, whether the evaluated subject perspires a lot at work, and how tired they feel after a day's work. In the leisure domain, the practices of physical activities during leisure are considered, such as exercises in the gym or practicing sports. In these domains, the following will be evaluated; the intensity of the physical exertion of these activities (mild, moderate, vigorous), the number of hours in the week in which these activities are practiced, and how long this physical activity has been practiced (<1 month, 1–3 months, 4–6 months, 7–9 months, > 9 months). In the field of occupational activities, the different physical activities in free time are considered, especially considering active displacement, such as the amount of time that is spent walking to the mall, market, or work; the time spent riding a bicycle is also considered.

At the end, this instrument offers a dimensionless score for each domain and the sum of the score of the 3 assessed domains determines the total amount of physical activity. This instrument has been used in different types of epidemiologic studies.^[14,15]^

### Cardiac autonomic modulation

2.6

The evaluation of cardiac autonomic modulation will be performed through HRV. For this evaluation, subjects will be instructed not to ingest alcoholic beverages and/or stimulants, such as coffee and tea, for 12 hours prior to the experimental protocol, to avoid influences on cardiac autonomic behavior.^[16]^

For this analysis, heart rate will be recorded beat-by-beat, using an Heart Rate Monitor (Polar V800, Finland), for 30 minutes at rest in a supine position, maintaining spontaneous breathing, in a room with a temperature between 21 and 24°C and relative air humidity between 50 and 60%.^[16]^ Only circulation of the evaluators will be allowed in the room during the execution of the HRV collection.

In the series of RR intervals obtained, 1000 intervals of the most stable stroke period will be analyzed, followed by digital filtering complemented by manual filtering to eliminate ectopic, artifacts, and premature beats. Only series with more than 95% sinus beat will be included in the study.^[17]^ The HRV analysis will be performed using linear methods (time and frequency domains) and non-linear methods.

For HRV analysis using linear methods, the RMSSD (square root of the square mean of the differences between adjacent normal RR intervals in a time interval expressed in milliseconds) and SDNN (standard deviation of the mean of all normal RR intervals, expressed in miliseconds) will be used for time domain analysis.^[18]^ For the analysis of HRV in the frequency domain, the spectral components of low frequency (LF: 0.04–0.15 Hz) and high frequency (HF: 0.15–0.4 Hz) will be used, in milliseconds squared (ms^2^) and normalized units (nu), as well as the ratio between these components (LF/HF). The spectral analysis will be calculated using the fast Fourier transform algorithm.^[18]^

The Poincaré plot (qualitative and quantitative analysis [SD1, SD2, and SD1/SD2 ratio]) will be utilized to analyze Heart Rate Variability using non-linear methods. The Poincaré plot is a graphical result formed by a map of points in Cartesian coordinates.^[19]^ The qualitative analysis of the plot will be performed by means of the analysis of the figures formed by the attractor, which were described by Tulppo et al.^[20]^ The quantitative analysis will be determined by the SD1 index (standard deviation of instantaneous beat-to-beat variability), SD2 index (long-term standard deviation of continuous R-R intervals), and SD1/ SD2 ratio.^[18]^

Kubios HRV Analysis software version 2.0 (Kupio University, Finland) and Visual Recurrence Analyzes (VRA) version 4.9 (Eugene Kononov, USA) will be used for analysis of linear and nonlinear methods.

### Socioeconomic level

2.7

The “Brazilian Economic Classification Criteria”, established in 2014 by the Brazilian Association of Research Companies,^[21]^ will be used to determine the economic condition of the participants. The questionnaire considers the degree of education, and the presence and quantity of certain rooms and domiciliary assets of the participant, and establishes the resulting classifications for economic condition: A1, B1, B2, C1, C2, and D - E. Subjects located in levels A1 and B1 will be classified as high socioeconomic class, those in classes B2, C1, and C2 as middle socioeconomic class, and those included in classes D and E as low socioeconomic class.

### Statistics analysis

2.8

After verification of normality by Shapiro-Wilks test, the variables characterizing the sample will be expressed as mean and standard deviation or median and interquartile range. The dependent variable will be the cardiac autonomic modulation. Pearson or Spearman correlation will be used to analyze the relationship between cardiac autonomic modulation and physical activity. Linear regression will evaluate the magnitude of the relationship between cardiac autonomic modulation and physical activity, both in the unadjusted model and in models adjusted by age, schooling, ethnicity, and socioeconomic status. Confounding variables will be inserted simultaneously into the model. It should be emphasized that linear regression analysis will be performed stratifying the study participants by sex. This same type of analysis will be performed to verify the possible relationships between the different domains of physical activity (work, leisure, and displacement activity) and cardiac autonomic modulation.

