## Introduction

1

Cardiac autonomic modulation has emerged as an important marker of cardiovascular health, providing early information on impairments in cardiovascular function. Disorders in the balance between the sympathetic and parasympathetic nervous system can cause a series of cardiovascular problems. Koopman et al,^[1]^ in an epidemiological study with about 800 African adults, found that low patterns of cardiac autonomic modulation were associated with higher odds of mortality.

Likewise, physical activity has been shown to improve autonomic function.^[2]^ Indeed, several studies have shown that physically active subjects present better cardiac autonomic modulation than physically inactive peers.^[3–5]^ Rennie et al^[3]^ evaluated the practice of physical activity through a questionnaire in English individuals aged 35 to 55 years-old and observed that those subjects who were classified as practicing more vigorous intensity PA presented better autonomic modulation than those located in the lower quartiles of PA intensity. Kaikkonen et al,^[4]^ in a study with 107 obese adults, observed that higher levels of physical activity assessed by means of a questionnaire were positively associated with the SDNN index in adults in Finland. However, Kang et al,^[5]^ in a study of 131 Korean male workers, observed that physical activity recorded in the study was inversely related to cardiac autonomic modulation.

However, some limitations have been pointed-out in the literature, namely the use of only one instrument (questionnaire or accelerometer) to assess physical activity. When an accelerometer is used, although it is possible to analyze the intensity, it is unlikely that the different domains of physical activity can be analyzed without additional information. In general, the different domains of physical activity are analyzed through questionnaires, namely in the work environment, leisure, and through active transport, for example. Thus, the ideal strategy is to use both types of measures of physical activity, enabling verification of which intensity and domain of physical activity tend to be better related to cardiac autonomic modulation. It is also emphasized that men and women tend to present different cardiac autonomic modulation^[6]^ and, thus, analysis stratified by sex should be considered in this relationship.

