### Sample

2.2

The sample will include adults aged 18 years or older from the city of Santo Anastacio, located in the southeastern region of Brazil, who are not injecting any type of medicine to control heart rate. Considering that the approximate population with over 18 years of age in the city of Santo Anastacio is 16000 inhabitants (IBGE), a correlation value of r = 0.23 was adopted to calculate the sample size,^[4]^ with an 80% power and 5% alpha, which determined a minimum sample size of 147 subjects.^[7]^ However, predicting possible refusals to participate in the study and losses of the subjects and data, a further 30% was added to the sample, totaling a minimum of 192 subjects to be evaluated. Conversely, as the present study will consider age, sex, and socioeconomic condition as adjustment variables, more 20 subjects was added for each adjustment variable. Thus, the final sample estimated is 252 individuals to be evaluated. The equation below was used to calculate the sample size. 
[figure not shown]

where n = sample size; Zα / 2 = alpha error value (1.96 [5%]); Zβ = beta error value (0.84 [20%]); r = correlation coefficient (Pearson or Spearman).

For sampling, the city of Santo Anastacio will be divided according to census sectors delimitation. This city has a total of 34 census sectors, of which 23 are in the urban area of the city and will be contemplated in this study. The number of people to be interviewed in each of the census tracts will be calculated based on the number of people residing in these sectors, considering the proportional population of each census sector – Table 1. In order to carry out this procedure, the census tracts will be divided based on a geographic map of the city of Santo Anastacio – Figure 1. The neighborhoods will be registered and numbered, as well as the streets and households. Subsequently, the neighborhoods, streets, and homes will be randomly drawn based on the “random” function of SPSS. Residents of the randomly selected households aged 18 or over will be considered eligible to participate in the study and invited to participate. If the selected individuals decline to participate in the research, a new household will be randomly selected, until complete the minimum sample size required for each census sector. This sample selection design was based on the 1st Design of the National Health Survey sample.^[8]^

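### The named dependent variable is a construct covering ten HRV indices, giving 160 to 180 sex-stratified adjusted slopes in a study sized on one unnamed correlation

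*Protocol article*

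**What the plan says.** On the outcome, section 2.8 states: "The dependent variable will be the cardiac autonomic modulation". It plans Pearson or Spearman correlations, then linear regressions, unadjusted and adjusted for age, schooling, ethnicity and socioeconomic status. The regressions are stratified by sex. The same analysis is repeated for the work, leisure and displacement domains.

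Section 2.6 supplies the numbers behind the construct. The time domain has SDNN and "the RMSSD (square root of the square mean of the differences between adjacent normal RR intervals". The frequency domain has LF and HF, each in ms² and in normalised units, and LF/HF. For the Poincaré plot: "The quantitative analysis will be determined by the SD1 index (standard deviation of instantaneous beat-to-beat variability", with SD2 and SD1/SD2 alongside.

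Section 2.4 gives counts per minute and time in four intensities. Section 2.5 gives three domain scores and their sum.

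On size, section 2.2 says "a correlation value of r = 0.23 was adopted to calculate the sample size", citing reference 4, "with an 80% power and 5% alpha, which determined a minimum sample size of 147 subjects". The next step was "a further 30% was added to the sample, totaling a minimum of 192 subjects to be evaluated", and then 20 subjects for each of three adjustment variables (age, sex, socioeconomic condition), giving 252. The Introduction reports of reference 4 that activity levels "were positively associated with the SDNN index in adults in Finland".

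The end of the Introduction states two directional hypotheses: higher intensity goes with better modulation, and leisure activity relates more strongly than other domains. Section 3 expects the results to inform health promotion.

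**The concern.** The sample size describes a study with one test, while the analysis describes a grid of them. A hypothesis about cardiac autonomic modulation can be met by any of ten indices, in men or in women, and nothing in the text says which result decides it. With that many slopes, some significant ones are expected even if activity and HRV are unrelated.

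Redundancy adds to this. RMSSD is listed under linear methods and SD1 under non-linear methods, but they carry the same information. A reader who sees both significant may count two findings where there is one.

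**Working it through.** **1. The plan's own figure.** Inputs from section 2.2: r = 0.23, two-sided 5% (z = 1.96), power 80% (z = 0.84). The Fisher z formula for one correlation is n = ((z_α/2 + z_β) / atanh r)² + 3.

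- atanh(0.23) = 0.2342.
- Unrounded z values: (2.8016 / 0.2342)² + 3 = 146.1, rounded up to 147. With 1.96 and 0.84 the result is 145.9, so 146. The stated 147 is reproduced.
- 147 × 1.30 = 191.1, rounded up to 192. Then 192 + 3 × 20 = 252.

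The figure is right for one correlation.

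**2. Counting the slopes.**

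- Indices: RMSSD, SDNN (2); LF ms², HF ms², LF nu, HF nu, LF/HF (5); SD1, SD2, SD1/SD2 (3). Total 10.
- Activity measures: counts per minute plus four intensity times (5); three domain scores (3); their sum (1). Total 9, or 8 if the total score is not analysed, since section 2.8 lists only the three domains.
- Adjusted slopes: 10 × 9 × 2 sexes = 180, or 10 × 8 × 2 = 160. Unadjusted models and correlations come on top.

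**3. Expected false positives under the global null, each slope at 5%.** 180 × 0.05 = 9; 160 × 0.05 = 8. This expectation does not depend on how the tests are correlated.

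The chance of at least one does depend on it. For 180 independent tests it is 1 − 0.95^180 = 99.99%. A null simulation with the ten indices tied by their formulas gave about 95%, with 9.1 false positives on average. It assumed 126 people per sex and activity measures independent of each other except for the total score. Real activity measures are correlated, so 95% is indicative only.

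**4. Redundancy.**

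- SD1 is the standard deviation of successive differences divided by √2. RMSSD is the root mean square of the same differences. As their mean is close to zero, SD1 = RMSSD/√2. In simulated 1000-beat series the largest deviation was 0.05%.
- If normalised units are shares of LF + HF, then HF nu = 100 − LF nu (correlation −1). LF/HF = LF nu / HF nu is then a monotone function of LF nu, so their Spearman results are the same.
- SD2² is approximately 2·SDNN² − RMSSD²/2 (largest relative error in SD2 0.22% in the same series). SD2 is thus a function of two other indices and not a copy of either.

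The ten indices rest on about four free quantities: RMSSD, SDNN, LF and HF.

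**5. What stratifying does to power.** Power = Φ(atanh(0.23)·√(n − 3) − z_α/2). An equal split by sex is assumed.

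| Analysed | Whole sample, 5% | One sex, 5% |
|---|---|---|
| 147 | 80% | 50% |
| 252 | 96% | 74% |

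The design power therefore belongs to a whole-sample test and not to the stratified regressions.

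**The case against.** The strongest reply is about scope. This is a condensed article. A multiplicity rule, and even the choice of lead index, could sit in an analysis plan or registry record that is not shown. That stands: the absence of a multiplicity procedure is not the point made here. The point rests on what the article does state, namely a construct fixed as the dependent variable and a sample size for one unnamed pair. The hypotheses are directional and meant to guide practice, so calling the work purely exploratory does not dispose of it.

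A reader might also infer more than the documents support:

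- **That all tests are planned at 5%.** Section 2.8 gives no test level. The 5% is a sample-size input, and the count of 8 to 9 is conditional on using it.
- **That SDNN is the index behind r = 0.23.** Section 2.2 cites the study that the Introduction describes as an SDNN result. It names no index or activity measure for the coefficient, and the Introduction gives no coefficient and does not say SDNN was the only index studied.
- **That linear and non-linear results must agree throughout.** Only SD1 and RMSSD are shown to be copies. The LF nu and HF nu identity needs the usual definition, which the article does not spell out. Nor does the article itself claim such agreement as independent confirmation.
- **That 147 is wrong.** It is not.

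Finally, the global null is a reference case. The Introduction cites earlier associations, so the true number of false positives may be lower.

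**Conclusion.** The concern holds as a mismatch between sections 2.2, 2.6 and 2.8. Followed as written, the plan fits 160 to 180 adjusted slopes with no lead index or exposure. At 5% each, about 8 to 9 would be significant by chance under the global null, and the hypotheses could be declared supported on any index or either sex. Agreement between RMSSD and SD1 is automatic; so is agreement between LF nu and HF nu under the usual definition.

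The size rests on three assumptions: 5% per slope, the global null, and eight or nine activity measures. Changing the last moves the count but not the conclusion. The matter should be corrected; it does not invalidate the design or the data to be collected.

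**What to change.** - **Section 2.8:** name one primary index. SDNN is the natural candidate because of how the Introduction describes reference 4.
- **Section 2.2:** state which index and activity measure r = 0.23 refers to.
- **Primary tests:** use one whole-sample model per hypothesis, adjusted for sex, which section 2.2 already lists as an adjustment variable. For intensity, pre-name one activity measure. For domain, put the standardised domain scores in one model and compare the leisure coefficient with the others. State this as a single contrast, because a leisure slope alone does not test a comparative claim. Apply Holm across the two tests.
- **Secondary results:** report the sex-stratified results and all other indices with estimates and confidence intervals. Do not count SD1 beside RMSSD, or HF nu and LF/HF beside LF nu, as separate evidence.

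The cost is fewer headline p-values; no new data are needed. Holm's first step at 2.5% needs 177 analysed for r = 0.23 at 80% power by the same formula, against 252 planned. If 30% of the 252 were lost, 252 × 0.70 = 176 would remain, about at that requirement. This covers a single correlation only. The power of the domain contrast cannot be worked out from the document's figures and should be stated separately.
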